ALT, Alanine Aminotransferase; AST, Aspartate aminotransferase; CDT, Carbohydrate-deficient transferrin; CSF, Cerebrospinal fluid; GT, Gamma-glutamyl transferase; Hb, Haemoglobin; HDL-C, High-density lipoprotein cholesterol; LDL-C, Low-density lipoprotein cholesterol; MCV, Mean Corpuscular Volume; NfL, Neurofilament light chain; PEF, Peak expiratory flow rate; WBC, white blood count.

**Table 3 T3:** Neurocognitive and psychiatric measurements assessed at baseline and after 12 and months respectively

Variable	Values/Information
Neurocognitive function: attention and processing speed	Trail making test part A (TMT-A)
	Symbol digit modalities test (SDMT)
	Simple reaction time test
Memory:	Rey auditory verbal learning test (RAVLT)
	CERAD word list learning test (CERAD)
	Corsi block-tapping test (CORSI)
Language:	Token test
	Boston naming test (BNT)
	FAS word fluency test (FAS)
	Cube drawing test
Visuospatial function:	Clock drawing test
Executive function:	Trail making test part B (TMT-B)
	Silent Stroop test
	Complex reaction time test
Psychological function	MADRS, MADRS-S
	MFS
	PCL-5
	PSS-14
	CGI-S
Overall health status and well-being	EQ-5D-5L
	EQ VAS

Participants’ neurocognitive functions will be assessed objectively with multiple tests facilitated through a digital platform provided by Mindmore AB by using two test batteries. All tests are based on validated neuropsychological rating scales. Raw neurocognitive test results will be compared with normative data for the Swedish population and converted to norm-calibrated scores: z-scores.^25^ The testing will provide a broad and deep neurocognitive profile of the patient and will assess the domains of attention and processing speed, memory, executive functions, visuospatial function and language.^25^
*Attention and processing speed* will be assessed by means of the Trail Making Test part A^26^ and Symbol Digit Modalities Test.^27^
*Memory* will be assessed by the 15-word Rey Auditory Verbal Learning Test (RAVLT),^28 29^ a 10-word auditory and visual learning test (CERAD Word List Learning Test)^30^ and a spatial memory test.^31^
*Language* will be assessed using the Token Test^32^ to measure auditory comprehension, the Boston Naming Test (BNT) – 15 words^33^ and, finally, the FAS Word Fluency Test.^34^
*Visuospatial functions* will be determined through the Cube Drawing Test^35 36^ and the Clock Drawing Test.^37 38^ Finally, *executive functions* will be assessed primarily through the TMT part B, measuring mental flexibility, and an in-house test of complex reaction time^23^ to measure information processing; additionally, a silent Stroop Test^39 40^ will measure concentration effectiveness. Task engagement and performance-based validity will be checked using two tests: Token Test and RAVLT, embedded into test batteries.

Complementary psychological examinations will be conducted at baseline, and at follow-up after 12 and 24 months, respectively. All tests used are validated instruments and translated into several languages. Patient-reported measurements will be obtained and registered digitally (Smart-Trial) in connection with the visit, which, if needed, will include an interpreter. Given the high symptom overlap between PTSD and common diagnoses such as depression, anxiety and ADHD, it is important for accurate diagnosis to assess the relationship between current symptoms and therefore we will use the Post-Traumatic Stress Scale (PTSD) PCL5.^41^

The Mental Fatigue Scale (MFS), which was constructed to capture the impact of mental fatigue on various life situations,^42^ is a self-assessment tool consisting of 14 defined symptoms of mental fatigue. Within each of the areas, the person rates the degree of impact on a 7-point scale, with support text provided for every other scale step. A total score is calculated. A score above 10.5 is considered mental fatigue of such a degree that it negatively affects functioning in daily life. Premorbid cognitive status will be checked using the Mini-mental state Examination Test.^43^

For premorbid depressive status mood examination, we will use the Montgomery Åsberg Test.^44^ The Montgomery-Åsberg Depression Rating Scale^44^ assesses and tracks changes in clinical depressive symptoms and is an interview-based instrument with 10 items corresponding to the main depressive symptoms, where each individual item is answered on a six-point scale depending on the severity of the depressive symptoms. The scale is specifically designed to track changes in depressive symptoms. For analysing the premorbid stress levels, we will use the PSS 14.^45^ Activity of daily living will be analysed using the EQ−5D- 5 L.^46^ To rule out symptoms related to Attention Deficit Hyperactivity Disorder (ADHD), we will use the screening battery of ASRS.^47 48^

Brain MRI will be performed at study inclusion and at the end of the study period, no later than 24 months from inclusion. The MRI system is a 3.0 Tesla scanner, and the examination protocol includes the following imaging acquisitions: structural T1 weighted (T1W), fluid attenuated inversion recovery (FLAIR), T2 weighted (T2W), susceptibility weighted (SWI), quantitative susceptibility mapping (QSM), diffusion tensor imaging (DTI), arterial spin labelling (ASL) and resting state functional MRI (rsfMRI). A structural report based on radiological findings will be provided by a neuroradiologist. The images acquired from the MRI examinations will enable us to do the following analyses: voxel-based morphology (VBM), functional and structural connectivity, cerebral blood flow (CBF), presence and extent of cerebral microbleeds in combination with QSM.

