## Methods

### Study design

The current study is a prospective cohort study which we have named PASC (post-acute sequel of COVID-19) 24. The study is exploratory in nature as the subject (neurocognitive symptoms after COVID-19 infection) is relatively new. No treatment will be given during the study period. Therefore, the research team has chosen not to perform randomisation nor blinding.

PASC 24 will be assessing and following recruited patients over a period of 24 months (figure 1). Three specific points of evaluation are planned, namely at baseline, after 12 months and 24 months. Recruitment began in 2024, and data collection is currently estimated to be completed by the end of 2026.

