### Study population (sample recruitment)

Participants in the PASC 24 study will principally be recruited primarily from Örebro County but may also be recruited from other areas of Sweden. There are approximately 300 000 inhabitants in Örebro County where the prevalence of SARS-CoV-2 is comparable to other parts of Sweden. A multidisciplinary conference (MDC) will ensure that the referred patients will have hitherto been given adequate and optimal care provision in Örebro County’s primary healthcare system (online supplemental file 1).

The overarching purpose is to detect and describe changes in physical, mental and cognitive function; daily activities and time-to-return to work in patients after experiencing moderate to severe COVID-19 infection. All patients will be living in the community and will be referred through their respective health centres to the MDC at the Department of Rehabilitation at the University Hospital Örebro with several health specialists, including cardiologists, geriatricians, neurologists and general practitioners.

All patients will be prescreened according to their premorbid cognitive and mood status by the PI ([name] specialist in psychiatry and geriatrics), so we can clearly indicate their premorbid status before inclusion in the study. Inclusion will be based on the definition from WHO (post COVID-19 condition (long covid)) concerning post covid syndrome, where the condition is characterised by a range of symptoms which usually start within 3 months of the initial COVID-19 illness and last at least 2 months. We will examine thoroughly patients’ medical records and check for a positive PCR test or positive antibodies in blood tests before inclusion.

Demographic data will be retrieved from medical records as well as in connection with inclusion: gender, age, medical diagnoses, medications, ethnicity, education, employment and degree of sick leave. Basic medical examination will be performed at inclusion: blood pressure, waist circumference, weight, BMI, and smoking habits (table 1).

**Table 1 T1:** Sociodemographic and medical details identified in recruited patients in PASC 24-study

Variable	Variable
Age	Years
Sex	Man/Woman
Language	Swedish/other
Tobacco	Never/Previously/Occasionally/Daily
Social status	Living alone/Living with partner
Occupation	Employed/unemployed/pensioner
Education	Secondary or vocational/Upper secondary/university
Land of birth	Sweden/other
Certified sick-leave	>3 months

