Certified sick-leave	Asthma/COPD/cancer/diabetes/heart insufficiency/hypertension/orthostatism/ hypercholesterolaemia/ neurological disorder/hypothyroidism/other
COVID-19 symptoms	Organ/specific symptoms
Smell/taste dysfunction	Remaining symptoms/previously

The *inclusion criteria* include COVID-19 infection confirmed by positive laboratory test (PCR test for SARS-CoV-2) taken during the acute infection, residual neurocognitive symptoms more than 3 months after the initial COVID-19 infection and an age of more than 18 years. Full-spectrum COVID severity cases will be included.

The *exclusion criteria* are severe cancer, dementia and ongoing alcohol or drug abuse. Included participants will then undergo baseline evaluation (figure 1). First when patients are included and have signed the patient consent form, they will then be tested using the neuropsychological tests tested via the digital platform Mindmore AB (www.mindmore.com).^23^ Mindmore is CE marked, approved, and purchased by the Research Centre of Region Örebro County. Trial participants may withdraw from the study at any time. Patients will receive no monetary compensation for study participation.

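### Three scales given after COVID-19 (MMSE, MADRS, PSS-14) are labelled as measures of premorbid status, although no assessment precedes the infection

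*Protocol article*

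**What the plan says.** Under Study population (sample recruitment), the article says that the principal investigator will prescreen each patient's cognition and mood, "so we can clearly indicate their premorbid status before inclusion in the study". Medical records are examined before inclusion. Diagnoses, medications, education and degree of sick leave are taken from the records or collected at inclusion. The inclusion criteria in the same section require "residual neurocognitive symptoms more than 3 months after the initial COVID-19 infection".

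Under Study design, the schedule is: "Three specific points of evaluation are planned, namely at baseline, after 12 months and 24 months".

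Under Variables studied, a scale is named for each premorbid construct:

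- Cognition: "Premorbid cognitive status will be checked using the Mini-mental state Examination Test".
- Depression: "For premorbid depressive status mood examination, we will use the Montgomery Åsberg Test".
- Stress: "For analysing the premorbid stress levels, we will use the PSS 14".

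The same section says of MADRS: "The scale is specifically designed to track changes in depressive symptoms". MADRS and PSS-14 also appear in Table 3, titled "Neurocognitive and psychiatric measurements assessed at baseline and after 12 and months respectively", and the text schedules the psychological examinations at baseline, 12 months and 24 months.

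**The concern.** Premorbid status means the state before the infection. A scale score from a patient who already has post-COVID symptoms describes the patient at that time. Unless the scale is deliberately asked about an earlier period, or put to an informant about that period, it cannot show what the patient was like before.

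The distinction matters more here than in many cohorts. The study has no control group, as its own list of limitations says. The Background asks for ways to tell PASC from other illness. The Discussion treats stress and frailty before infection as an open question and hopes to describe risk factors. Valid pre-infection information is one of the few means this design has of separating what was already there from what followed the infection. If depression or stress that arose after COVID-19 is reported as premorbid, a possible effect of the disease appears in the results as a cause of it or a predisposition to it.

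**Working it through.** The plan attaches no figure to this point, so there is nothing to reproduce. The check sets the timing against the labels.

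1. **Earliest possible measurement.** Patients reach the study by referral after COVID-19, and inclusion requires symptoms persisting beyond 3 months. Prescreening comes before inclusion, but that is not before infection, because the patients prescreened are already being referred for the condition.

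2. **Distance of each visit from infection.** With entry more than 3 months after infection, the baseline visit lies more than 3 months after it, the 12-month visit more than 3 + 12 = 15 months, and the 24-month visit more than 3 + 24 = 27 months. None of the three visits can yield a pre-infection score.

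3. **Could the scales be used retrospectively?** The article describes no recall period before the infection, no altered wording and no informant version for MMSE, MADRS or PSS-14. What it says of MADRS, that it is built to follow change, points to a measure of current state.

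4. **Does the same scale have a second role?**

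| Scale | Called premorbid | In Table 3 as a repeated measure |
|---|---|---|
| MMSE | yes | no |
| MADRS | yes | yes |
| PSS-14 | yes | yes |

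The label is wrong for all three. For MADRS and PSS-14 there is also a conflict of roles: the inclusion score is described as the state before the disease and is also the first point of the series that follows the disease.

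5. **Is there another source of premorbid status?** Records are reviewed, and some of the items collected can pre-date the infection. But the article does not name records as the source of premorbid cognition, mood or stress; it names the scales.

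6. **Where could the label do harm?** First, in description: a table of premorbid depression and stress would contain post-infection scores. Second, and only if it were done, in adjustment: if current mood is partly a result of PASC, treating it as a pre-infection confounder means conditioning on a possible consequence of the disease, which can distort the association between a biomarker and symptoms. The direction and size depend on correlations among biomarker, mood and cognition that the document does not give.

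**The case against.** The strongest reply is that this is a slip of wording with little behind it. The study is exploratory, no sample size, test or eligibility cut-off depends on the word premorbid, and relabelling would not change one data point. A specialist prescreens the patients and reviews the records, so real pre-infection information may well be collected. A repeated scale normally supplies both a baseline value and follow-up values, and a baseline MADRS or PSS-14 score is a sound prognostic variable for later change in neuropsychological z-scores, whatever it is called.

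Much of this stands. Repeating a scale is no fault, and prognostic use of the baseline value is legitimate. The record review makes the remedy easy. It does not rescue the text, which assigns the three premorbid constructs to scales and not to records. Nor is this a detail that an analysis plan could fill in: it is a positive statement of what named instruments measure, and no later document can turn a post-infection score into a pre-infection one.

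A reader might go further in three ways that the document does not support.

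- **That the scores are planned as risk factors, confounders or screens.** The Statistical analysis section names no predictors, and the exclusion criteria contain no cut-off on any of these scales. Such use is conceivable, given the interest in stress and risk factors, but it is not stated.
- **That the ADHD screen (ASRS) has the same fault.** It is never called premorbid. It is offered for differential diagnosis, which is a separate question.
- **That a given share of a biomarker association would be lost.** Any percentage would rest on assumed correlations, on an adjustment that is not stated, and on mood lying on the pathway.

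**Conclusion.** The point holds as an error of measurement timing and labelling that should be corrected before analysis. All three scales assigned to premorbid status yield post-infection values at every planned assessment, and two of them, MADRS and PSS-14, are also repeated study measures. Followed as written, the plan would report post-infection status as pre-infection status in an uncontrolled cohort that wants to describe risk factors and to tell PASC from other illness.

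The conclusion rests on the stated entry criterion and visit schedule, and on the absence of any retrospective or informant administration from the article. If the full protocol describes such an administration, the conclusion would have to be revisited for the scale concerned. Possible bias in biomarker-symptom associations is conditional on these scores being used as pre-infection covariates, and no size can be given for it.

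**What to change.** - Call MMSE, MADRS and PSS-14 at inclusion baseline (post-infection) status throughout, and reword the prescreening sentence so that it does not promise premorbid status from these scores.
- Define premorbid status only from information dated before the infection in the medical records already reviewed (diagnoses, medications and sick leave), together with education. Some of these items may also be collected at inclusion, so each needs a date relative to the infection; the PCR test required for entry can supply the reference date.
- State that the inclusion scores will not be interpreted, or adjusted for, as pre-infection variables. Their use as baseline prognostic values for later change can stay.

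The cost is relabelling and one dated set of variables abstracted from the charts, with no added visit, test or burden on participants. Data collection is expected to run to the end of 2026, so the change can be made before the final analysis. The downside is small: chart data are coarser than scale scores, and earlier problems that never reached the records will be missed.

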### Statistical analysis

Data will be processed using SPSS (version 22). Before performing statistical analysis, all data will be scrutinised for quality, distribution and missing data. Descriptive statistics (means, medians, frequencies and percentages) will be used to characterise the data. Differences between independent groups will be analysed using independent t-test for continuous outcomes and Pearson’s χ^2^ test or Wilcoxon Signed Rank Test will be used to find associations between two categorical/ordinal variables. Regression or repeated measures ANOVA (or other applicable method) will be used to test neuropsychological change over time (z-score change) to find the independent variables significant to the outcome.

Statistical significance will be set at p<0.05.

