## Abstract

**Abstract:**

**Introduction:**

Knowledge about the late effects of COVID-19, or so-called post-acute sequelae of COVID (PASC), and its pathogenesis is still very limited. The purpose of this observational study is to chart late neurocognitive effects of the COVID-19 infection. The aim is to increase knowledge of the underlying biological processes and describe how biomarkers correlate with degree of symptoms, mapping their role as diagnostic markers over time (24 months).

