### Sample size calculation

The aim is to offer participation in the study to all patients in Örebro County who meet the inclusion criteria. Therefore, the sample size calculation has not been rigorously applied.

However, we have performed calculations based both on previous estimates of the frequency of PASC^10^ and on statistical considerations regarding future analyses. In both cases, we have concluded that a group of approximately 50–100 participants will be possible to recruit and provides space for meaningful analysis. The ethical permission applies to up to 100 participants.

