There are many conflicting issues concerning PASC. This includes the role of common biomarkers in the determination of risk for developing PASC or indeed, the role of stress and pre-infection frailty.^58 59^ Additionally, there is an impending need for long-term studies to further explore and analyse the interrelationship between PASC and the commonly reported ‘brain-fog’ correlated to cerebral structural changes.^60^,^62^

Our current study may have some limitations. Acceptance for the PASC condition has diminished regionally, nationally and internationally creating difficulties in both recruitment and handling of patients.^63^ This has very real consequences in terms of resource allocation devoted to this patient group. There are clear methodological challenges in diagnosis differentiation, as noted in many studies.^64^ Predicting the dropout rate is extremely difficult as we are not aware of any other study results with repeated lumbar puncture in patients with

PASC, though another similar study reported attrition rates of up to 40%.^65^ Finally, it is our intention that by using a comprehensive, multi-modular assessment of individuals with symptoms related to the debut of SARS-CoV-2 infection, we might further describe and understand the symptomatology, risk and prognostic factors of PASC and how these individuals perform over a 2-year period of follow-up. This might contribute to the establishment of adequate systems of patient management.

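### The Wilcoxon signed-rank test is named for association between two categorical or ordinal variables, a question it does not address; wherever it is chosen over chi-square, the result would mislead

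*Protocol article*

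**What the plan says.** The Statistical analysis section of the protocol article assigns methods to three tasks.

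- Independent groups, continuous outcome: "Differences between independent groups will be analysed using independent t-test for continuous outcomes".
- Two categorical or ordinal variables: Pearson's chi-square is named first, and then, as the alternative, "Wilcoxon Signed Rank Test will be used to find associations between two categorical/ordinal variables".
- Change over time: "Regression or repeated measures ANOVA (or other applicable method) will be used to test neuropsychological change over time (z-score change").

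The threshold is given as "Statistical significance will be set at p<0.05", with no statement of one or two sides. The Sample size calculation section expects that "a group of approximately 50–100 participants will be possible to recruit and provides space for meaningful analysis". The Abstract gives as part of the aim to "describe how biomarkers correlate with degree of symptoms".

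**The concern.** The signed-rank test takes two measurements of the same quantity on the same person, subtracts one from the other, and asks whether the differences are centred at zero. Association is a different property: whether people who are high on one variable tend to be high (or low) on the other. Two variables can be strongly associated and have the same location, or be unrelated and have different locations.

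The section's wording leaves no use for which the named test fits:

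- Taken literally, as association, the test does not address the question.
- Taken with the opening of the sentence, which concerns independent groups, a paired test is applied to unpaired data. The counterpart there is the rank-sum (Mann-Whitney) test.
- Taken as change within a person, it conflicts with the next sentence, which gives change over time to regression or repeated measures ANOVA.

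Table 1 supplies a concrete case. Tobacco use has four ordered levels and education three. A signed-rank test of the two would subtract an education code from a tobacco code, and its p-value would depend on how the categories are numbered. At stake are associations reported between unrelated variables and real associations missed, in whatever ordinal pairs are analysed this way.

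**Working it through.** The article gives no figure for this point, so there is nothing to reproduce. The check is what the named test does when it is used for the stated purpose.

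**Inputs from the article**
- n = 50 and n = 100 (Sample size calculation).
- n = 60, from the Discussion's remark that "another similar study reported attrition rates of up to 40" per cent: 100 × (1 − 0.40) = 60.
- Significance level 0.05 (Statistical analysis).

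**Assumptions, not in the article**
- Two-sided testing.
- Two 5-level variables cut from a bivariate normal at −0.84, −0.25, 0.25 and 0.84, which puts about 20% in each level.
- Latent correlation ρ of 0, 0.5 or 0.7.
- Second margin either equal to the first or with cut points moved by 0.5 SD.
- 2,000 samples per setting, so a true 5% rate has Monte Carlo standard error √(0.05 × 0.95 / 2000) = 0.5 percentage points.

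**The test.** With D = X − Y for each person and m non-zero differences, W⁺ is the sum of the ranks of |D| over the people with D > 0. It is referred to mean m(m+1)/4 and variance m(m+1)(2m+1)/24, corrected for ties. The correlation of X and Y does not enter the hypothesis. When the pair is exchangeable, as with equal margins here, D is symmetric about zero at every ρ, so the null hypothesis is true however strong the association is.

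**(a) Equal margins: percentage of samples rejecting**

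| n | ρ | Signed-rank | Spearman | Chi-square |
|---|---|---|---|---|
| 50 | 0 | 4.5 | 5.5 | 4.6 |
| 50 | 0.5 | 4.3 | 91.9 | 45.7 |
| 50 | 0.7 | 4.8 | 99.9 | 92.8 |
| 60 | 0 | 4.9 | 4.0 | 4.1 |
| 60 | 0.5 | 4.1 | 96.9 | 55.4 |
| 60 | 0.7 | 5.3 | 100.0 | 97.1 |
| 100 | 0 | 5.3 | 4.9 | 5.6 |
| 100 | 0.5 | 5.9 | 99.8 | 86.1 |
| 100 | 0.7 | 5.0 | 100.0 | 100.0 |

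The signed-rank column stays at about 5% throughout.

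**(b) Independent variables (ρ = 0), margins 0.5 SD apart.** The shifted margin has category probabilities of about 0.09, 0.14, 0.17, 0.23 and 0.37. Its mean level is 0.09 + 0.28 + 0.51 + 0.92 + 1.85 = 3.65, against 3.00 for the other variable. The differences are therefore off zero although the variables are unrelated.

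| n | Signed-rank | Spearman | Chi-square |
|---|---|---|---|
| 50 | 62.3 | 5.4 | 3.3 |
| 60 | 69.0 | 4.7 | 4.7 |
| 100 | 88.9 | 5.5 | 4.6 |

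Repeat runs with other seeds, and one with wider cut points (−1.5, −0.5, 0.5, 1.5: 64%, 74% and 91%), keep the signed-rank figure within about 61–92%.

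**(c) Independent scores on scales with different ranges.** With assumed means of 15 and 28 and SD 8, the signed-rank test rejects in 100% of samples at n = 50 and at n = 100. Spearman rejects in 5–6%.

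**The case against.** The strongest reply is that the clause also names Pearson's chi-square, which does test association. It holds its level in the runs above (3–6% under independence) and has 46%, 55% and 86% power at ρ = 0.5. An analyst who always chose chi-square would make no error of this kind, only lose power by ignoring order. This stands, and it confines the point to analyses in which the signed-rank test is the one chosen.

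A reader might infer that the study's main biomarker–symptom correlations would be uninterpretable. The article does not support that. Most of the biomarkers, such as NfL, the cytokines, kynurenic acid, tau and amyloid, are quantitative, and the clause covers pairs of categorical or ordinal variables. The Mental Fatigue Scale is used as a total score. The neurocognitive tests become z-scores, and their change over time goes to regression, repeated measures ANOVA or another suitable method.

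A reader might also object that no rank correlation is named. In a condensed article, with any analysis plan not shown, that absence is no finding. The finding is that a test is named for a purpose it cannot serve.

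Finally, the name may be a slip for the rank-sum test, and the study describes itself as exploratory and gives no treatment. Both are fair and bear on severity. Neither corrects the text, and an analyst who follows it would run the wrong test.

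**Conclusion.** The point holds in a limited form. The signed-rank test is wrongly assigned, nothing else in the article corrects it, and any ordinal-by-ordinal association analysis run with it would be misleading in both directions. Under the assumed 5-level scales and n = 50–100, it has no power beyond about 5% when margins are equal, and it declares an association in about 61–92% of samples when the variables are independent with margins 0.5 SD apart.

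The two results differ in firmness. The first needs equal margins but does not depend on the sample size or on the strength of the association. The second depends on the assumed margins: it falls towards 5% as they coincide and approaches 100% for scales with very different ranges. Since the article gives no ordinal distributions, no single false-positive rate can be attached to this study.

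This should be fixed. It does not undermine the design, and no sample-size figure rests on it.

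**What to change.** Reassign the tests in the Statistical analysis section, for example:

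> Association between two ordinal variables will be assessed by Spearman or Kendall rank correlation, and between two nominal variables by Pearson's chi-square test. An ordinal outcome will be compared between two independent groups by the Mann-Whitney (rank-sum) test. The Wilcoxon signed-rank test will be used only for paired change in the same variable between two visits.

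The sentences on the t-test and on regression or repeated measures ANOVA need no change for this purpose. The cost is a few lines of wording. No additional data or participants are needed. The Study design section estimates that data collection will be completed by the end of 2026, so the change can be made before the final analysis.
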